## Enrolment

### Inclusion criteria

All participants who met the following criteria were included: (1) diagnosed with CSM and underwent surgery between 24 h and 3 months prior to enrolment; (2) aged between 20 and 75 years of either sex; (3) a Japanese Orthopaedic Association (JOA) score of 5 to 15; (4) no less than a primary school education; (5) no cognitive dysfunction; and (6) understood the study, agreed to participate in the study, and signed the informed consent form.

### Exclusion criteria

Participants were excluded if they met any of the following conditions: (1) contraindications for magnetic resonance imaging (such as a cardiac pacemaker, cardiac stent, artificial heart valve, bone fracture fixation plate, or claustrophobia); (2) concurrent limb fractures, degenerative diseases of the lumbar or thoracic vertebrae, cerebrovascular disease, other neurological disorders, intraspinal space-occupying lesions, history of cervical trauma, previous cervical spine surgery, hip or knee joint diseases, or other serious systemic diseases; (3) severe cardiopulmonary dysfunction; or (4) pregnant or lactating.

### Withdrawal or dropout criteria

In this study, the intervention measures for both the trial group and the control group may be stopped if the subject meets any of the following criteria: (1) the subject requests to withdraw from the clinical study; (2) the subject is unable to complete the relevant test as needed, which affects the data collection; (3) the subject receives other treatments during the treatment period without authorization; (4) the subject experiences adverse events or serious adverse events during the trial that require their withdrawal from the study; (5) the subject experiences significant worsening of the disease, complications or special physiological changes that require their withdrawal from the study; (6) the researcher considers it unsuitable for the subject to continue participating in this study.

### Who will provide informed consent?

All eligible postoperative patients with cervical spondylotic myelopathy (CSM) were informed about the methods and objectives of this study as well as the potential benefits and risks involved. Patients were provided with an informed consent form for review and signing.

### Intervention

Interventions using VR technology were conducted on the GRAIL system (Netherlands Motek Medical Company SY02097646), with all participants undergoing diagnostic assessment by a professional spine specialist or rehabilitation medicine physician prior to participation to ensure suitability. The training time was scheduled in accordance with the GRAIL guidelines to ensure that the VR intervention was appropriate and safe, as it has been shown to be the most effective intensity of training for patients with CSM. All intervention measures were implemented by qualified therapists, and the participants’ reactions were recorded after each intervention. Safety measures were taken to prevent harm to all participants.

### Conventional rehabilitation group

Patients in the rehabilitation group underwent a programme that focused primarily on strength training to improve their performance ability and coordination [21]. The postoperative limb muscle strength, sensation, and motor function of patients was assessed to develop a functional training program based on existing problems. The program included the following exercises: (1) finger extension and forceful bending and gripping movements were repeated 5–10 times, and the frequency of training sessions was appropriately increased. (2) Patients were guided in performing active knee and hip joint movements 3 times a week for 15 min each 24 h after surgery. (3) Straight leg lift exercises were performed 2 times a week for 15 min each. (4) Isometric contraction exercises, such as those involving the quadriceps femoris, were performed 3 times a week for 10 min each. (5) Ankle joint dorsiflexion and plantar flexion exercises were performed 3 times a week for 15–20 min each. (6) Walking training was performed 3 times a week for 10–20 min each time.

### Outcomes

Prior to the intervention, individuals who expressed interest in participating in the study were invited to schedule an appointment for additional information.

If they choose to participate, they will sign an informed consent form and be screened by independent researchers to determine if they meet the inclusion and exclusion criteria. Participants who meet all the inclusion criteria and none of the exclusion criteria will be included in the study. Descriptive data, including general information such as age, sex, race, occupation, height, weight, body mass index (BMI), blood pressure, education level, medical history, medication use, smoking status, drug use, and alcohol consumption, will be carefully collected before randomization. In addition, all participants were assessed using three scales: the JOA, the VAS, and the NDI.

Both the intervention group and the control group completed a total of 12 rehabilitation sessions over a period of 4 weeks. Outcomes will be assessed immediately after the 4-week intervention period and compared with baseline data. The primary outcome will be the change in functional ability, assessed using a standardized functional assessment tool (JOA score). The secondary outcome measures will include pain level (VAS score), neck disability (NDI score), and changes in the functional areas of the brain.

### Measurements

Figure 2 lists the schedule of all study assessments and the timeframe in detail. The assessments are described briefly below:

#### Primary outcome measurement

The primary outcome measure was the change in the JOA score for the cervical spine. The JOA score consists of a total of 17 points, with 4 points each for upper and lower limb motor function, 2 points each for upper and lower limb and trunk sensation, and 3 points each for bladder function. Patients were assessed using the JOA score before intervention, after intervention, and during follow-up in accordance with the JOA evaluation criteria for cervical spine disease treatment established by the Japanese Orthopaedic Association. The results were categorized into five groups: > 75% excellent, 50–74% good, 20–49% fair, 0–19% no change, and < 0 deterioration.

#### Secondary outcome measures

The secondary outcome measures consisted of the VAS score, NDI score, and neuroimaging data. The data will be collected at the baseline assessment and at the end of the intervention (4 weeks after randomization).

#### Visual analogue scale (VAS)

The VAS pain consists of a 100-mm horizontal line with the words “no pain” and “worst possible pain” at the line’s ends. Patients were asked to quantify their neck pain by drawing a vertical mark on the area of the horizontal line that best represented their pain level during the preceding 24 h.

#### Neck disability index (NDI) score

The NDI measures disability related to neck pain and includes 10 items related to neck pain intensity, personal care, lifting, reading, headache, concentration, working, sleeping, driving, and recreation. Each item is scored from 0 to 5, with higher scores indicating more severe disability. The results are interpreted as follows: 0–20% indicates mild disability, 21–40% indicates moderate disability, 41–60% indicates severe disability, 61–80% indicates very severe disability, and 81–100% indicates complete disability or the need for further examination to rule out symptom exaggeration.

#### Neuroimaging scans

The data for this study were collected at the Radiology Department of Yueyang Hospital of Integrated Traditional Chinese and Western Medicine, which is affiliated with the Shanghai University of Traditional Chinese Medicine. Participants were positioned in the supine position, and their heads were secured using a specially designed head mask. All magnetic resonance imaging (MRI) scans were performed using a Siemens Magnetom Verio 3. T MRI scanner. Resting-state functional MRI (fMRI) data were obtained using a single-shot echo-planar imaging (EPI) sequence with interleaved scanning of 43 slices, a flip angle of 90°, a matrix of 64 × 64, a TR of 300 ms, a slice thickness of 3.0 mm, an FOV of 230 × 230 mm^2^, and a gap of (voxel size of 3.6 × 3.6 × 3.0 mm^3^). T1-weighted structural scans were obtained using a weighted fast spoiled gradient-echo (FSPGR) sequence with TR/TI/TE of 190/900/2.93 ms, a flip angle of 9°, an FOV of 256 × 256 mm^2^, a slice thickness of 1.0 mm, a matrix of 256 × 256, and an average of 1.0. All assessments involving scales and MRI scans were conducted prior to the intervention and then repeated after 4 weeks of intervention.

### Safety assessment

Any adverse events such as discomfort caused by MRI procedures, headache, or VR training that cannot be tolerated will be recorded throughout the intervention period and reported to the ethics committee to ensure safety. Operators conducting GRAIL procedures should be familiar with the trial protocol and procedures related to safety, and ethics must strictly follow the Grail operation guidelines. In case of an adverse event during the intervention, the participant will receive appropriate medical care, and all the details will be recorded and reported to the principal investigator and ethics committee to determine if the participate should continue the trial. All collected adverse events will be truthfully reported in future publications, and the incidence rate of adverse events will also be considered in the analysis.

### Sample size calculation

The goal of our study was to investigate the effectiveness of VR technology in the rehabilitation of patients with CSM after surgery. Due to a lack of research on the effect of VR technology on the rehabilitation of CSM patients after surgery, we conducted a small-sample pilot study. The sample size was estimated based on the improvement in JOA scores for cervical spondylosis reported by the Japanese Orthopaedic Association. One month after surgery, the average JOA scores and SDs for the VR rehabilitation intervention group (*n* = 10) and the conventional rehabilitation group (*n* = 10) were 15.30 (SD = 0.90) and 14.7 (SD = 0.78), respectively, with an effect size (Cohen’s *D*) of 0.71. Using the Gpower 3.1 software, we calculated the needed sample size, which, with a type I error of *α* = 0.05 and a type II error of *β* = 0.2, was estimated to be a sample size of *n* = 64. Considering a dropout rate of 20%, 39 participants were needed for each group, for a total of 78 participants. Finally, we randomly allocated the 78 participants into a VR training combined with rehabilitation intervention group and a conventional rehabilitation group, each consisting of 39 participants.

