## Method/design

### Study design

The aim of this randomized controlled trial was to investigate the effectiveness of virtual reality (VR) technology in the postoperative rehabilitation of patients with CSM. A total of 78 eligible patients were recruited and randomly assigned to either the routine rehabilitation group or the VR training combined with routine rehabilitation group (1:1). The primary outcome will be measured with the Japanese Orthopaedic Association (JOA) (Table 1) cervical myelopathy evaluation scale, and the secondary measures will include the visual analogue scale (VAS), neck disability index (NDI), and functional magnetic resonance imaging (fMRI) scans [18–20]. The intervention will be implemented in accordance with a standardized protocol, and independent researchers will execute and supervise the random allocation of patients in the trial. The study protocol is in compliance with the SPIRIT recommendation. For the SPIRIT checklist, see Additional file 1, and the study design is presented in Figs. 1 and 2. This study is an exploratory investigation.

**Table 1 Tab1:** Japanese Orthopaedic Association (JOA) score for patients with cervical myelopathic

Motor function	
Upper extremity	
The thumb and fingers	
0 [Complete disturbance] The patient cannot use chopsticks or a spoon/fork, and cannot fasten a button on his or her own.	
1 [Severe disturbance] The patient cannot use chopsticks or write, and can barely use a spoon/fork.	
2 [Moderate disturbance] The patient can pick up a large object with chopsticks but can hardly write. He/she can fasten a large button.	
3 [Slight disturbance] The patient makes awkward use of chopsticks, writes in a clumsy manner, but can fasten buttons on his/her shirt.	
4 [Normal] Normal	
Lower extremity	
0 [complete disturbance] The patient cannot stand or walk alone.	
(0.5 The patient can stand up.)	
1 [Severe disturbance] The patient needs support to walk on a flat surface.	
(1.5 The patient can walk on a flat surface without any support but the walking is not stable.)	
2 [Moderate disturbance] The patient can walk on a flat surface without any support, but needs a handrail to walk up and down stairs.	
(2.5 The patient can walk on a flat surface without any support, but needs a handrail only to walk down stairs.)	
3 [Slight disturbance] The patient can walk fast, although awkwardly.	
4 [Normal] Normal	
Sensory function	
Upper extremity	

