0 [Severe disturbance] Complete sensory loss (touch sensation, pain sensation)	
(0.5 Partial sensory loss ≤ 5/10 (touch sensation, pain sensation); intolerable pain or numbness)	
1 [Moderate disturbance] Partial sensory loss ≥ 6/10 (touch sensation, pain sensation); numbness and hypersensitivity.	
(1.5 [Slight disturbance] Slight numbness (normal sensation))	
2 [Normal] Normal	
Trunk	
0 [Severe disturbance] Complete sensory loss (touch sensation, pain sensation)	
(0.5 Partial sensory loss ≤ 5/10 (touch sensation, pain sensation); intolerable pain and numbness)	
1 [Moderate disturbance] Partial sensory loss ≥ 6/10 (touch sensation, pain sensation); numbness and hypersensitivity.	
(1.5 [Slight disturbance] Slight numbness (normal sensation))	
2 [Normal] Normal	
Lower extremity	
0 [Severe disturbance] Complete sensory loss (touch sensation, pain sensation)	
(0.5 Partial sensory loss ≤ 5/10 (touch sensation, pain sensation); intolerable pain and numbness)	
1 [Moderate disturbance] Partial sensory loss ≥ 6/10 (touch sensation, pain sensation); numbness and hypersensitivity.	
(1.5 [Slight disturbance] Slight numbness (norm sensation))	
2 [Normal] Normal	
Urinary bladder function	
0 [Severe disturbance] Urinary retention, incontinence	
1 [Moderate disturbance] Feeling of residual urine, straining of oneself, dull urination, elongation of urination (retarded urination), urinary incontinence	
2 [Slight disturbance] Retarded urination, pollakisuria	
3 [Normal] normal	
Total 17

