### Randomization and allocation concealment

After the baseline evaluation, each eligible participant was randomly assigned to either the intervention group or the control group at a 1:1 ratio. The random allocation cards will be generated using the random permutation principle with a random number table generated by SPSS21. These cards will be placed in opaque envelopes, with the envelope numbers corresponding to the card numbers. The envelopes will be opened in the order of the participants’ visits, and the participants will be randomly assigned to either the conventional rehabilitation group or the conventional rehabilitation combined with VR training group based on the grouping specified on the card inside the envelope. This method of random allocation will ensure that the assignment is unbiased and that each participant has an equal chance of being assigned to either group.

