### Statistical analysis

All nonimaging data will be analysed using SPSS version 21 by an independent statistician who is blinded to the treatment and control groups to ensure objectivity and reduce bias. The statistical significance level for testing will be set at 0.05 with a two-tailed test. Continuous variables are presented as the mean, standard deviation, or maximum or minimum values based on their statistical distributions. Independent sample *t* tests or nonparametric tests (Mann–Whitney *U* test) will be used to compare the results presented as continuous variables and mean values to validate the effectiveness of the intervention. Furthermore, intra- and intergroup comparisons were made at 4 weeks to observe the differences between the two intervention methods. If necessary, logistic regression, general linear correlation, or regression was used to compare different types of results based on the variable type and distribution. Basic data comparisons between the treatment and control groups will be performed using *t* tests, chi-square tests, or nonparametric tests. Participants who drop out during the intervention period will not be excluded according to the intention-to-treat principle, and missing data will be replaced using the last observation carried forward method to maintain statistical power and avoid bias.

The amplitude of low-frequency fluctuation (ALFF) is an indicator of the amplitude energy of the low-frequency spectrum and reflects the spontaneous activity of neurons in the resting state of the brain. The ALFF is a useful tool for analysing functional MRI data to study longitudinal neural changes and explore the relationship between brain plasticity and the recovery of sensory and motor function induced by stimulation [22]. In this study, the REST 1.9 software from Beijing Normal University (http://www.restfmri.net/) was used to perform linear drift and calculate the amplitude of signal oscillation in each voxel in the low-frequency range (0.01–0.1 Hz) to obtain ALFF images. Finally, the ALFF values of each participant were *Z*-transformed for further statistical analysis.

Longitudinal measurements in a resting-state task and further correlation analysis of imaging and scale score data obtained from baseline and postintervention measurements were performed to explore the relationships between brain remodelling and postoperative sensory and motor function recovery in CSM patients.

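### The pilot SDs behind the sample size appear to divide by n rather than n−1; if so, Cohen's d is 0.6755 and 72 evaluable patients, not 64, are needed for 80% power

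*Protocol article*

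**What the plan says.** The section Sample size calculation of the protocol article reports one-month postoperative JOA scores from a pilot with "intervention group (*n* = 10) and the conventional rehabilitation group (*n* = 10"). The means and SDs "were 15.30 (SD = 0.90) and 14.7 (SD = 0.78), respectively". From these it takes a Cohen's d of 0.71 and, "with a type I error of *α* = 0.05 and a type II error of *β* = 0.2", a required total of 64, raised to 78 (39 per arm) for 20% dropout. It does not say which divisor the SDs use.

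The section Statistical analysis fixes the test: "The statistical significance level for testing will be set at 0.05 with a two-tailed test", and "Independent sample *t* tests or nonparametric tests (Mann–Whitney *U* test) will be used". Allocation is 1:1.

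Table 1, under Study design, sets the grain of the score. Items are scored in whole points, with half points in the lower-extremity motor item ("0.5 The patient can stand up") and in the sensory items ("1.5 [Slight disturbance] Slight numbness (normal sensation"). A total therefore moves in steps of 0.5 at the finest.

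**The concern.** Power planning needs an estimate of the population SD, so the sum of squares about the mean should be divided by n−1. With ten observations, dividing by n makes the SD too small by a factor of √(9/10) = 0.949. That inflates d by √(10/9) = 1.054 and understates the number of patients needed.

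The article does not show the pilot data, but ten scores on a half-point scale with a known mean can produce only a discrete set of SDs. The printed values can be compared with that set, and they fit the divide-by-n form and not the n−1 form. At stake are the effect size, the 64 evaluable patients and the 80% power, all of which rest on these two SDs.

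**Working it through.** **Inputs.** Means 15.30 and 14.7, SDs 0.90 and 0.78, n = 10 per arm, alpha 0.05, power 0.80, 64 evaluable, 78 in total, 20% dropout (Sample size calculation); two-sided t test (Statistical analysis); half-point scale with maximum 17 (Table 1).

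**1. The plan's own figure.** Pooled SD = √((0.90² + 0.78²)/2) = 0.8421. d = 0.6/0.8421 = 0.7125. A two-sided two-sample t test (noncentral t) needs 32 per arm, 64 in total, with power 80.1%. The stated chain reproduces, so the printed SDs went straight into it. (Entering d rounded to 0.71 would give 66.)

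**2. Attainable sums of squares (SS).** SS = Σx² − (Σx)²/10.
- VR arm: Σx = 153, so SS = Σx² − 2340.9.
- Conventional arm: Σx = 147, so SS = Σx² − 2160.9.

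With half-point scores and these totals, Σx² moves in steps of 0.5, so SS runs …, 5.1, 5.6, 6.1, 6.6, 7.1, 7.6, 8.1, … in both arms. With whole points only, it moves in steps of 2: …, 4.1, 6.1, 8.1, ….

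**3. Which divisor fits the printed SDs?**

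| Arm | Printed SD | Divisor | SS range that rounds to it | Attainable SS in range |
|---|---|---|---|---|
| VR | 0.90 | 9 | 9×0.895² to 9×0.905² = 7.21 to 7.37 | none; neighbours 7.1 (SD 0.888), 7.6 (SD 0.919) |
| VR | 0.90 | 10 | 8.01 to 8.19 | 8.1 (SD 0.900) |
| Conventional | 0.78 | 9 | 9×0.775² to 9×0.785² = 5.41 to 5.55 | none; neighbours 5.1 (SD 0.753), 5.6 (SD 0.789) |
| Conventional | 0.78 | 10 | 6.01 to 6.16 | 6.1 (SD 0.781) |

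The two divide-by-n matches can be reached with whole-point scores alone:
- {14,14,15,15,15,15,16,16,16,17} has mean 15.3 and SS 8.1.
- {14,14,14,14,14,15,15,15,16,16} has mean 14.7 and SS 6.1.

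**4. Figures with divisor n−1.** SDs: √(8.1/9) = 0.949 and √(6.1/9) = 0.823. Pooled SD = √((8.1 + 6.1)/18) = 0.888. d = 0.6/0.888 = 0.6755.

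| | d = 0.7125 (printed SDs) | d = 0.6755 (n−1 SDs) |
|---|---|---|
| Evaluable per arm for 80% power | 32 (64 in total) | 36 (72 in total) |
| Power, 32 per arm | 80.1% | 75.8% |
| Power, 31 per arm (78 × 0.8 = 62.4, so 62) | 78.8% | 74.4% |
| Power, 39 per arm (all 78) | 87.4% | 83.8% |

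The 36 per arm needs the unrounded 0.6755; entering 0.68 gives 35 per arm (70).

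**5. Sensitivity to the control arm.** If 14.7 is a rounded 14.65 (Σx = 146.5), SS = 5.525 is attainable and √(5.525/9) = 0.784, so 0.78 could be an n−1 SD.
- Correcting the VR arm alone and keeping the 0.6 difference: √((0.949² + 0.78²)/2) = 0.868, d = 0.69, 34 per arm (68), power 77.7% with 32 per arm.
- Carrying the 14.65 through, the difference becomes 0.65. With SDs 0.949 and 0.784, d = 0.65/0.870 = 0.747, and 60 patients in total suffice.

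**The case against.** The divisor is nowhere stated and the 20 scores are not shown, so everything depends on reading the printed digits literally. The article is not consistent about digits: 15.30 stands beside 14.7. A control mean of 14.65 reopens n−1 in that arm. A VR SD of 0.9 padded to 0.90 would admit n−1 values of 0.888 and 0.919, which removes the exclusion in the other arm. A divide-by-n match alone is also weak evidence: on the half-point grid the matching SS ranges are about 0.18 and 0.16 wide against steps of 0.5, so each arm would match by chance roughly one time in three. All of this stands, and it is why the point is an inference to be confirmed. What carries the inference is that n−1 fails in both arms, as printed, while divide-by-n fits both.

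It can also be said that the shift is small. An approximate 95% interval for d from ten per arm runs from −0.19 to 1.62, and the study calls itself exploratory. That limits the weight of the point, but it does not justify keeping a stated d, n and power that do not follow from the pilot data.

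Three stronger readings are tempting and are not supported:
- A reader might infer that a calculation error is proven. It is not. The printed chain from SDs to 64 is arithmetically sound, and only the SDs are in doubt.
- A reader might infer that the planned 78 have only 74–76% power. Those figures are for 62 to 64 evaluable patients. The Statistical analysis section keeps dropouts in by last observation carried forward, and with all 78 analysed power is 83.8%, provided that the carried-forward values do not dilute the effect.
- A reader might infer that these powers apply to the primary outcome. That outcome is the change in JOA score, whereas the pilot figures are one-month levels, so nothing here gives the power for change.

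**Conclusion.** The concern holds as a probable, not a proven, error. Taken as printed, both pilot SDs are incompatible with n−1 and compatible with n. If that is confirmed, d falls from 0.71 to 0.6755, the evaluable number for 80% power rises from 64 to 72 (8/64 = 12.5%), and power at 64 evaluable patients falls by about 4 points, from 80.1% to 75.8%.

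This assumes ten valid Table 1 totals per arm, means of exactly 15.30 and 14.70, SDs genuinely given to two decimals, no typing error, and a two-sided t test on one-month levels. The size is moderate. It is a correction to stated figures and gives no ground for enlarging the trial.

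**What to change.** Recompute both SDs from the 20 pilot scores with divisor n−1, and report means and SDs to the same number of decimals. If they come out at 0.949 and 0.823, restate the section Sample size calculation as follows:
- d = 0.6755, given unrounded so that the sample size can be reproduced;
- 36 evaluable patients per arm (72) for 80% power;
- power of 75.8% with 64 evaluable patients and 74.4% with 62 (78 less 20% dropout), noting that 83.8% applies only if all 78 are analysed with an undiluted effect;
- a sentence saying that these figures are for a comparison of one-month JOA levels, not for the change-score primary outcome.

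Keep the 78. If the scores show that n−1 was used after all, correct the printed digits and leave the rest. The cost is one recalculation and, if confirmed, a slightly less favourable stated power; no extra patients and no design change are needed.

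### The 80% power was computed from SDs of one-month JOA levels, while the primary outcome is change in JOA, so it is not established for that endpoint; the 20% dropout step is also slightly short.

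*Protocol article*

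**What the plan says.** The section Sample size calculation says that the estimate rests on improvement in JOA. The figures it gives are scores at one time point: "One month after surgery, the average JOA scores and SDs for the VR rehabilitation intervention group" and for the conventional group "were 15.30 (SD = 0.90) and 14.7 (SD = 0.78), respectively", with 10 patients in each. From these it takes d = 0.71, a "type I error of *α* = 0.05" and a "type II error of *β* = 0.2", and arrives at 64 patients. It then adds the dropout allowance: "Considering a dropout rate of 20%, 39 participants were needed for each group, for a total of 78 participants".

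The section Primary outcome measurement defines a different quantity: "The primary outcome measure was the change in the JOA score for the cervical spine". The section Outcomes agrees, since it compares the assessment after the 4-week intervention with baseline.

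The section Statistical analysis fixes the level and sidedness: "The statistical significance level for testing will be set at 0.05 with a two-tailed test". It names an independent-samples t test or a Mann–Whitney U test and group comparisons at 4 weeks. It does not say whether the change or the 4-week score is tested. Dropouts stay in the analysis with last observation carried forward (LOCF).

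Patients enter with a baseline JOA of 5 to 15, having had surgery in a wide window: "underwent surgery between 24 h and 3 months prior to enrolment".

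**The concern.** The variance of a change score depends on the baseline SD, the final SD and the correlation between them. The plan uses only the final SD. Nothing ties the resulting 80% to the endpoint that the plan defines.

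The pilot SDs are narrow (0.90 and 0.78 on a 17-point scale), whereas eligibility allows ten points of baseline JOA and up to three months since surgery. If baseline scores vary much more than 4-week scores, an unadjusted comparison of change carries that extra variation and loses power. The team would then be relying on an 80% that its own test does not have, and a null result could be read too confidently as absence of effect.

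The dropout step raises a smaller question: whether 78 randomised patients leave the 64 that the calculation asks for.

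**Working it through.** **Inputs from the protocol article**
- Means 15.30 and 14.7, SDs 0.90 and 0.78, d = 0.71, α = 0.05, β = 0.2, N = 64, dropout 20%, final N = 78 (Sample size calculation).
- Two-sided test (Statistical analysis) and 1:1 allocation (Randomization and allocation concealment).
- Not given: baseline SD, SD of change, correlation ρ between baseline and 4-week JOA. The values used for these below are assumptions.

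**1. Reproducing 64**
- Difference = 15.30 − 14.7 = 0.60.
- Pooled SD = √((0.90² + 0.78²)/2) = 0.842.
- d = 0.60/0.842 = 0.7125.
- Two-sample t test, noncentral t, two-sided 0.05: 32 per arm gives 80.1%. So N = 64 reproduces, and it does so with the SDs of final levels alone.

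**2. Power for unadjusted change**

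SD of change = √(s_B² + s_F² − 2ρ·s_B·s_F), with final SD s_F = 0.842 and baseline SD s_B. The expected between-group difference in change is still 0.60, because randomisation balances baseline on average. With 32 per arm:

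| Assumed baseline SD | Assumed ρ | SD of change | d = 0.60/SD | Power |
|---|---|---|---|---|
| 0.84 | 0.7 | 0.65 | 0.92 | 95% |
| 0.84 | 0.5 | 0.84 | 0.71 | 80% |
| 1.5 | 0.9 | 0.83 | 0.72 | 81% |
| 1.5 | 0.7 | 1.09 | 0.55 | 58% |
| 1.5 | 0.5 | 1.30 | 0.46 | 44% |
| 2.0 | 0.9 | 1.30 | 0.46 | 45% |
| 2.0 | 0.5 | 1.74 | 0.35 | 27% |

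One bound needs no value for ρ. The SD of change cannot be smaller than |s_B − 0.842|. To keep 80% it must be about 0.842 or less, so a baseline SD above about 0.842 + 0.842 = 1.68 puts power below 80% at every correlation. At baseline SD 2.0 even ρ = 1 gives an SD of change of 1.158 and power of only 53%.

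**3. Power for the 4-week score adjusted for baseline (ANCOVA)**

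Residual SD = 0.842 × √(1 − ρ²). With 32 per arm, ignoring the one degree of freedom spent on the covariate:
- ρ = 0: 0.842, power 80%
- ρ = 0.3: 0.803, power 84%
- ρ = 0.5: 0.729, power 90%
- ρ = 0.7: 0.601, power 98%

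Baseline SD does not enter. Under the plan's own difference and final SD, this analysis holds about 80% or more.

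**4. Dropout**
- The plan's figure: 32 × 1.2 = 38.4, rounded up to 39 per arm, 78 in total.
- Completers after 20% loss: 78 × 0.8 = 62.4, about 31 per arm, power 78.8%.
- Number needed for 64 completers: 64/0.8 = 80.
- Loss that 78 can absorb: 1 − 64/78 = 17.9%.

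**The case against.** The strongest reply is that the plan may test 4-week scores after all. The section Statistical analysis speaks of comparisons at 4 weeks, and if the 4-week score is what goes into the t test, the calculation matches it. A statistical analysis plan, not shown, might settle this. The reply stands in part: it is why one cannot say that the calculation contradicts the test. It does not remove the problem, because two other sections define the outcome as change, and the sample-size section itself describes its basis as improvement.

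A reader might infer that the true power is not 80%, or is probably far lower. The documents do not support that. They give no baseline SD and no correlation, and the table in the working runs from 27% to 95%. The JOA range of 5 to 15 is an eligibility limit, not an observed spread. It makes a wide baseline plausible, no more.

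The remedy can also be challenged. It keeps the final SD at 0.842 while the worry is that trial patients are more varied than the pilot. That is fair: if the 4-week SD turns out larger, ANCOVA loses power as well, and the stated 80% has to carry that condition.

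On dropout, it can be said that LOCF keeps all 78 in the analysis, so the count of 62 does not arise. With 39 per arm and no dilution, power would be 87.4%. But carried-forward values can dilute the effect: as an illustration, if 20% of patients contribute no effect and the SD is unchanged, d becomes 0.8 × 0.7125 = 0.57 and power is about 70%. Either way, the allowance as written does not deliver 64 completers.

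A reader might also fault the reliance on a 10 versus 10 pilot. The article states the pilot's size, means and SDs, explains that prior research is lacking and calls the study exploratory. That is disclosed and is not an error in the plan.

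**Conclusion.** The concern holds in this form: the 80% was derived for the JOA level at one time point and is not established for change in JOA, the endpoint that the plan defines. The sample-size section also mislabels its own basis. The size of any loss cannot be fixed from the documents. With difference 0.60, final SD 0.842 and 32 per arm, power on unadjusted change falls below 80% at every correlation once the baseline SD exceeds about 1.68; with a narrower baseline, it may lie on either side of 80%, depending on the correlation.

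The dropout slip is real but small: 2 patients (80 against 78) and 1.3 percentage points of power (80.1% to 78.8%) on a completer basis. It would not merit a point on its own.

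**What to change.** - Make the 4-week JOA score, adjusted for baseline JOA by ANCOVA, the primary analysis, and say so in the outcome and analysis sections. This settles which quantity is tested and matches the inputs of the calculation.
- In the sample-size section, replace the reference to improvement. State that the 80% refers to the 4-week JOA score with difference 0.60 and assumed SD 0.84, and that power is lower if the trial's 4-week SD is larger.
- If unadjusted change is kept as the primary analysis, restate power over a range of baseline SDs and correlations, as in the working.
- Correct the dropout sentence: 78 randomised tolerates 17.9% loss for 64 completers, or gives about 79% power with 20% loss on a completer basis.

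The cost is wording and a documented amendment before the data are analysed; the article reports that recruitment was still under way. Baseline and 4-week JOA are already collected, and no extra patients are needed. The price is that the stated power becomes openly conditional and, on the dropout line, slightly less favourable.
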